## Outcome measures

Table 2 summarizes the schedule of enrollment, interventions, and assessments for participating providers. Clinician-centered, implementation outcomes from the reach, effectiveness, adoption, implementation, and maintenance (RE-AIM) framework [67], see also re-aim.gov, include reach, adoption, and maintenance (sustainability). Provider reach is defined as the ratio of providers who provide informed consent to participate and complete the COAST training over the number of providers who received information about the trainings via emails, personal invitations, and other communication means targeting behavioral health providers. Patient reach is defined as the ratio of patients who consent to use the app relative to the number of patients deemed eligible to use the app. Adoption is defined as the ratio of newly trained providers who initiate the use of the COAST platform with patients (i.e., provide a patient with an app code) over the total number of providers who completed the COAST training (i.e., trained users + trained non-users). Sustainability is determined by comparing the frequency of COAST platform use by the trained providers across the three groups at the 3-, 6-, and 12-month assessments to measure potential changes on these domains over time.

**Table 2 Tab2:** Providers’ schedule of enrollment, interventions, and assessments for this hybrid type 3 implementation-effectiveness randomized trial

			Study period				
	Enrollment	Consent	Baseline	Post-randomization			
**Timepoint**	***-t***_***1***_	**0**	***t1***	***Familiarization***	***3 months***	***6 months***	***12 months***
**Enrollment:**	X						
Complete sleep training	X						
Informed consent		X					
NOCTEM COAST training			X				
Randomization			X				

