## Randomization of providers

After completing the COAST training and 10- to 14-day familiarization period, providers will be randomized in a 1:1:1 manner to one of three implementation strategies: COAST only, COAST+EF, or COAST+EF/IF (implementation strategies are further described below). Providers will be randomized within participating sites to one of the three facilitation conditions. A computer-generated randomization schedule based on a permuted block design will be created a priori. Using a permuted block design ensures that there will be equal numbers in each arm. The allocation will follow the generated sequence and the local research point of contact will inform the providers of their assignment at the end of the familiarization period, prior to patient enrollment.

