The first hypothesis is that providers randomized to one of the two COAST+ conditions will show greater reach, adoption, and sustainability at the 3- and 12-month follow-ups compared to providers randomized to the COAST only. For adoption, we will use a test for two proportions to determine whether reach and adoption differ between COAST versus COAST+EF and COAST+EF/IF at the 3- and 12-month follow-ups. With at least 8 providers in COAST and 16 in COAST+EF and COAST+EF/IF, as well as a reach and adoption between 0.50 and 0.60 in COAST, we will have 0.80 power (alpha = 0.05) to detect a difference in proportions between COAST and COAST+ of 0.39–0.46. For sustainability, each provider’s average number of interactions per patient over time and number of newly enrolled patients each month for each of the 12 months will be computed. We will then fit a generalized linear mixed effects model to regress number of interactions on group (COAST versus COAST+) and time. The group-by-time interaction will also be tested. Models will include a random intercept and time effect. With six repeated measures (autocorrelation 0.60–0.80) and 24 providers (8 COAST and 16 COAST+EF and COAST+EF/IF), we expect 0.80 power (alpha = 0.05) to detect differences of 0.99–1.11 between groups. With 12 repeated measures, we expect power to detect differences of 0.97–01.10 between groups.

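### Provider reach is settled before randomization and cannot differ by arm; patient reach can be compared, but the two-proportion test powered on 8 and 16 providers does not fit it

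*Protocol article*

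**What the plan says.** Outcome measures gives two definitions of reach.

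- Provider reach: "Provider reach is defined as the ratio of providers who provide informed consent to participate and complete the COAST training". Its denominator is every provider who was told of the trainings, by whatever route.
- Patient reach: "Patient reach is defined as the ratio of patients who consent to use the app relative to the number of patients deemed eligible".

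Randomization of providers fixes the timing: "After completing the COAST training and 10- to 14-day familiarization period, providers will be randomized in a 1:1:1 manner". The local contact is then to "inform the providers of their assignment at the end of the familiarization period, prior to patient enrollment".

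The first hypothesis, in Objective, aims, and hypotheses and again in Statistical analyses plan and power calculations, sets the facilitated arms against COAST only: "providers randomized to one of the two COAST+ conditions will show greater reach, adoption, and sustainability at the 3- and 12-month follow-ups". Reach is its part (a).

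For the test, the statistical section says "we will use a test for two proportions to determine whether reach and adoption differ between COAST versus COAST+EF and COAST+EF/IF". The power sentence begins "With at least 8 providers in COAST and 16 in COAST+EF and COAST+EF/IF, as well as a reach and adoption between 0.50 and 0.60", with that range applying to the COAST-only arm, and arrives at a detectable difference of 0.39–0.46 with power 0.80 and alpha 0.05. Neither sentence says which of the two reach measures is meant, or whether the unit is the provider or the patient.

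**The concern.** A between-arm comparison needs an outcome that every randomized unit can still have or not have after allocation. Provider reach is not such an outcome, because the act it counts (consenting and completing training) is an entry condition for randomization. Facilitation, which starts afterwards, cannot change it.

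That leaves patient reach. It is measured after randomization and is a sensible target for facilitation, but the only test named for reach is a two-proportion test sized on providers, and this does not match a proportion of patients within providers.

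The trial is a hybrid type 3 design whose main focus is the comparison of implementation strategies, and reach is the first-listed part of its first hypothesis. If the text stays as it is, the analyst must choose the reach measure, the unit and the model after the fact, and one of the available choices (pooling patients) would overstate the evidence.

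**Working it through.** **1. Can provider reach differ by arm?** Put the definition beside the sequence of events.

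- Denominator: providers who were informed about the trainings. This group is formed before consent. Those who do not go on to enrol are never randomized, so they cannot be counted in any arm's denominator.
- Numerator: providers who consented and completed COAST training. The text makes both a precondition of randomization.
- Restricted to randomized providers, reach is 8/8 = 1.00 in COAST and 16/16 = 1.00 in the two facilitated arms combined. The difference is 0 by construction.
- The numerator counts per arm are set by the 1:1:1 allocation (24/3 = 8 per arm), not by any effect of facilitation.

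A COAST-arm value of 0.50–0.60 is therefore impossible for provider reach. Table 2 and the text differ on whether familiarization comes before or after randomization, but this does not matter here. Familiarization is not part of the definition, and invited providers who do not enrol have no arm in either order.

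**2. What does the stated power figure describe?** Inputs from the statistical section: n = 8 and 16, COAST proportion 0.50–0.60, power 0.80, alpha 0.05 (sidedness not stated).

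Power = Σ over a, b of Bin(a; 8, p1) × Bin(b; 16, p2) × 1{|z(a, b)| ≥ 1.96}, where z is the pooled two-proportion statistic.

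- p1 = 0.50: smallest difference with 80% power is 0.460 (power 0.800 at 0.50 v 0.96).
- p1 = 0.60: smallest difference is 0.387 (power 0.821 at 0.60 v 0.99).

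This reproduces 0.46 and 0.39. The calculation treats each provider as one independent yes/no result. Adoption is such a result, because each trained provider either does or does not start using COAST with a patient. Provider reach has no variation (step 1), and patient reach is not one yes/no per provider.

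**3. Does the named test fit patient reach?** There are two readings.

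*Providers as units (n = 8 and 16).* Each provider contributes a rate, consenting over eligible patients. A test for two proportions does not apply to a set of rates.

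*Patients pooled.* The test applies in form but ignores the provider, which is the unit of randomization. The size of that error can be shown under stated assumptions.

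- The article plans at least 36 enrolled patients per provider. Enrolled patients are the numerator of patient reach. The denominator is eligible patients, so m = 36/reach: 36/0.60 = 60 and 36/0.50 = 72 (assumed from the article's own range).
- ICC for reach: not given. The 0.01 in the article belongs to the non-inferiority power statement for the Insomnia Severity Index (ISI). Assumed range: 0.01–0.10.
- Design effect DE = 1 + (m − 1) × ICC. True two-sided error of a nominal 5% test = 2 × [1 − Φ(1.96/√DE)]. Cluster sizes are taken as equal.
- Example: m = 72, ICC 0.01: DE = 1 + 71 × 0.01 = 1.71; 1.96/√1.71 = 1.50; error = 0.134.

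The last column is the difference detectable with 80% power once clustering is counted (pooled normal approximation, effective sizes 8m/DE and 16m/DE, COAST reach 0.50 for m = 72 and 0.60 for m = 60).

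| m | ICC | DE | True error | Detectable difference |
|---|---|---|---|---|
| 72 | 0.01 | 1.71 | 0.134 | 0.093 |
| 60 | 0.01 | 1.59 | 0.120 | 0.094 |
| 72 | 0.05 | 4.55 | 0.358 | 0.150 |
| 60 | 0.05 | 3.95 | 0.324 | 0.145 |
| 72 | 0.10 | 8.10 | 0.491 | 0.197 |
| 60 | 0.10 | 6.90 | 0.456 | 0.187 |

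With clustering ignored (ICC 0) the detectable difference would be 0.072 (m = 72) or 0.075 (m = 60).

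**The case against.** The strongest defence is that reach in the first hypothesis must mean patient reach. The comparison is set at the 3- and 12-month follow-ups, and provider reach cannot change with follow-up. On that reading H1(a) has a usable post-randomization outcome. The authors plainly know about nesting, since they put a random provider effect in the ISI models, and the exact model for patient reach is detail that an article may leave to a fuller plan.

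Much of this stands. Patient reach is a legitimate comparative outcome, so it would be wrong to infer that H1(a) cannot be tested at all. A reader might also infer that the plan commits to pooling patients and hence to an inflated false-positive rate. The article does not say that. The only sample sizes given beside the test are numbers of providers, so the error rates in the working are conditional on a choice that the article leaves open. Nor is the 0.39–0.46 figure wrong, since it reproduces for a yes/no result per provider.

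What the defence does not remove is the conflict in the text. The article defines provider reach as a reach outcome, hypothesizes a difference in reach between randomized arms without excluding it, and states power for reach on 8 and 16 providers. It also names a test for reach that fits patient reach under neither choice of unit. These are statements that do not agree, not detail left for later.

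**Conclusion.** The point holds in two parts of different strength.

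Provider reach cannot be compared between arms. This follows from the definition and the time of randomization and needs no assumption. Its implied place in the first hypothesis, and any reading of the power sentence as covering it, should go.

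Patient reach can be compared, but the stated test and sample sizes do not fit it. If patients were pooled, the nominal 5% error would be about 12–13% at ICC 0.01, 32–36% at 0.05 and 46–49% at 0.10. These figures assume 60–72 eligible patients per provider, equal cluster sizes and ICCs that the article does not give for reach. They show why the unit must be fixed in advance. They are not a forecast of what the trial will do.

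**What to change.** - Report provider reach once, descriptively, for the whole trial. Remove it from the first hypothesis and from the power sentence.
- Name patient reach as the H1(a) outcome, with provider clustering in its analysis: a logistic mixed model with a random provider intercept and small-sample degrees of freedom, or a comparison of provider-level rates.
- Restrict the 0.39–0.46 power statement to adoption.
- If power is stated for patient reach, give the assumed ICC and the number of eligible patients per provider.

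The cost is wording and a different analysis of counts that the definitions already require; no new data are needed. The downside is that H1(a) then rests on patient reach alone, and any power statement for it depends on an ICC that has to be assumed.

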**Interventions:**							
COAST only							
COAST + external facilitation (EF)							
COAST + EF + internal facilitation (EF/IF)							
**Assessments:**							
Demographics and practice survey			X				
Post-training survey			X				
Organization readiness for implementing changes			X			X	X
System usability scale			X	X		X	X

Fidelity is evaluated by quantifying the adherence (or discrepancy) between algorithm-recommended interventions relative to interventions that are sent to patients by providers. As in some cases there may be valid clinical reasons why a provider determines a patient should not receive the algorithm-recommended intervention (e.g., sickness, incompatible with assigned duties), we expect a rate of non-adherence of approximately 20%—noting we will not be accessing patients medical records to validate the potential reasons for deviations.

The primary patient-centered outcome measure of treatment effectiveness is the Insomnia Severity Index (ISI [32]). Other symptom domains to be assessed are summarized in Table 3, and include the PTSD Checklist-5 (PCL-5 [47, 48]), the 8-item Patient Health Questionnaire (PHQ-8 [49]) to assess symptoms of depression, the 7-item Generalized Anxiety Disorder scale of the PHQ (GAD-7 [50]), the PEG, a 3-item validated and reliable pain measure [68], and the 4-item PROMIS Satisfaction with Social Roles and Activities [69]. For patients, the total time required to complete the battery is approximately 20 min. The battery will be completed through the NOCTEM app at baseline, post-treatment, and again 3 and 12 months post-treatment.

**Table 3 Tab3:** Self-report measures of sleep and daytime symptoms to be completed by participating patients at baseline, post-intervention, and at the follow-up assessments

Domain	Scale	Number of items	Time to complete
**Sleep**			
Insomnia	Insomnia Severity Index (ISI)	7	< 3 min
Perceived global improvement	Patient self-report Global Improvement Scale (PGI)	1	< 1 min
Clinician-rated global improvement	Clinician-rated Global Improvement Scale (CGI)	3	< 3 min
**Daytime symptoms**			
Daytime sleepiness	Epworth Sleepiness Scale (ESS)	8	< 1 min
Posttraumatic stress disorder (PTSD)	PTSD Checklist (PCL-5)	20	< 3 min
Depression	Patient Health Questionnaire (PHQ-8)	8	< 3 min
Anxiety	Generalized Anxiety Disorder (GAD-7)	7	< 3 min
Pain	Pain, Enjoyment, General activity (PEG)	3	< 1 min
Functioning	Satisfaction with Social Roles and Activities	4	< 1 min

## Statistical analyses plan and power calculations

Preliminary data analyses (e.g., descriptive statistics, correlations, principal component analysis) will be performed prior to hypothesis testing to check for collinearity of covariates and outcome measures, to ensure completeness and accuracy of data, and to evaluate distributions. Missing observations will be investigated to determine the underlying mechanism (missing at random, completely at random, not at random) so that appropriate methods for handling the missing data can be employed. Namely, if data are missing at random, we will use multiple imputation (MI) to ensure that any individuals with missing covariates or outcome data can be included in the analysis sample. However, if data are found to be missing not at random, we will use methods that explicitly model this type of nonrandom missingness (e.g., pattern mixture models) and perform sensitivity analyses evaluating the impact of the missingness. Power was computed using PASS statistical software and documentation. Each model will include covariates including study site, patient age and sex, military rank, and use of psychotropic medication (yes/no). Masked data will be provided to the biostatistician who will perform the analyses. Randomization will be unmasked only after analyses are finalized.

The first hypothesis is that providers randomized to one of the two COAST+ conditions will show greater reach, adoption, and sustainability at the 3- and 12-month follow-ups compared to providers randomized to the COAST only. For adoption, we will use a test for two proportions to determine whether reach and adoption differ between COAST versus COAST+EF and COAST+EF/IF at the 3- and 12-month follow-ups. With at least 8 providers in COAST and 16 in COAST+EF and COAST+EF/IF, as well as a reach and adoption between 0.50 and 0.60 in COAST, we will have 0.80 power (alpha = 0.05) to detect a difference in proportions between COAST and COAST+ of 0.39–0.46. For sustainability, each provider’s average number of interactions per patient over time and number of newly enrolled patients each month for each of the 12 months will be computed. We will then fit a generalized linear mixed effects model to regress number of interactions on group (COAST versus COAST+) and time. The group-by-time interaction will also be tested. Models will include a random intercept and time effect. With six repeated measures (autocorrelation 0.60–0.80) and 24 providers (8 COAST and 16 COAST+EF and COAST+EF/IF), we expect 0.80 power (alpha = 0.05) to detect differences of 0.99–1.11 between groups. With 12 repeated measures, we expect power to detect differences of 0.97–01.10 between groups.

The second hypothesis is that COAST+EF and COAST+EF/IF will yield greater improvements in patient insomnia symptom severity than COAST only over the acute 6-week intervention period. We will compute the change in ISI from baseline to 6 weeks (∆ISI = baseline ISI − 6-week ISI), with higher ∆ISI values indicating a greater improvement over time. We will use a mixed effects model to regress ∆ISI on group, accounting for nesting within providers through a random effect and including relevant covariates. We will extract estimates from the model to compute the standardized mean difference *d* [70, 71] and 95% confidence interval between COAST and COAST+ (EF; EF/IF) accounting for patients nested within providers. Second, using a mixed effects model with a random clinician effect, we will regress ISI at baseline and 6 weeks of treatment (COAST versus COAST+EF and COAST+EF/IF), time, and their interaction, controlling for relevant covariates. A significant treatment-by-time effect will indicate that the change in ISI differs between COAST and COAST+EF and COAST+EF/IF. Assuming an average of 12 providers per group (8 in COAST and 16 in COAST+EF and COAST+EF/IF) and 36 patients per clinician, we expect 0.80 power (alpha = 0.05) to detect a standardized mean difference of 0.232 between groups. We will also evaluate the extent to which COAST+EF is not inferior to COAST+EF/IF as measured by changes on the ISI over the acute 6-week intervention period. This non-inferiority hypothesis will be tested with the general form—H_0_: COAST+EF is inferior to COAST+EF/IF versus H_1_: COAST+EF is non-inferior to COAST+EF/IF. Using the methods described above, we will compute the standardized mean difference *d* and 95% confidence interval [*d* (95% CI)] for COAST+EF − COAST+EF/IF of ∆ISI. As positive values of ∆ISI indicate more improvement, a positive *d* is in favor of COAST+EF and a negative *d* is in favor of COAST+EF/IF. We will use a non-inferiority margin (NIM) of − 0.50 and declare COAST+EF to be non-inferior to COAST+EF/IF if the lower bound of the 95% CI for *d* is > − 0.50. We will declare COAST+EF to be inferior to COAST+EF/IF if the lower bound of the 95% CI for *d* is ≤ − 0.50. For example, if *d* (95% CI) = − 0.10 (− 0.40, 0.20), we would declare COAST+EF as non-inferior to COAST+EF/IF because − 0.40 > − 0.50. However, if *d* (95%CI) = − 0.40 (− 0.70, − 0.10), we will declare COAST+EF to be inferior because − 0.70 ≤ − 0.50. These one-sided decision rules equate to requiring the effect size of the COAST+EF to COAST+EF/IF comparison to have no more than moderate strength (|d| = 0. 5), in favor of COAST+EF/IF. The NIM of |d| = 0.5 set to determine non-inferiority is stringent as it represents 50% of the effect size reported in recent meta-analyses [50, 72, 73]. Assuming 8 providers per group and 36 patients per clinician, an intra-class correlation of 0.01 [74], a non-inferiority margin of 0.50, and a true difference of δ = 0, we expect > 0.99 power to reject our null hypothesis and conclude that COAST+EF is non-inferior to COAST+IF/EF.

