Prior to the enrollment of providers and patients, the NOCTEM team and the EFs and IFs will first complete an in-depth review of written guidelines and standard operating procedures for this project. During the trial, the EF and IF teams will meet monthly by phone and communicate via email, as needed, between scheduled monthly meetings to address any issues that arise and share newly acquired information. The EF and IF guidelines will be updated as needed to make sure both processes are documented and kept up to date during the trial.

The sleep intervention is the same for all patients enrolled by participating clinicians. When a disordered sleep pattern is detected by the NOCTEM algorithms (usually within 7 days), the provider will receive automated sleep recommendations for each patient and will be asked to review and confirm prior to forwarding it to the patient. Recommendations are consistent with stimulus control, sleep restriction, and other EB-BSM techniques, including suggested times for rise time and bedtime and exercise to minimize nightmares. Providers may elect to modify the algorithm-driven recommendations as they see fit, based on knowledge of their patients. Patients will receive their provider-approved, personalized behavioral sleep recommendations on a weekly basis. This process will be repeated for the next 4 to 6 weeks.

Participating patients will not be terminated from the study until (1) they decide to stop using the app; or (2) their provider deems that a different treatment or referral is required; or (3) the treatment course is complete, and the use of the app is no longer necessary; or (4) the end of the project. COAST is not commercially available, and patients who wish to remain in sleep treatment will be encouraged to discuss options with their provider. Because the COAST system requires that a provider monitors entries and sleep status and progress, the app will be disabled when a patient is no longer in the care of a provider. This will avoid misleading patients that they are still under the care of the provider through the app only.

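### The MNAR models and sensitivity analyses are triggered by a finding (MNAR rather than MAR) that observed data cannot supply

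*Protocol article*

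**What the plan says.** All of the missing-data plan is in the Protocol article, section Statistical analyses plan and power calculations. It has three steps.

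- **Diagnosis.** "Missing observations will be investigated to determine the underlying mechanism (missing at random, completely at random, not at random".
- **MAR branch.** "if data are missing at random, we will use multiple imputation (MI", covering missing covariates and outcomes. No sensitivity analysis is attached to this branch.
- **MNAR branch.** "if data are found to be missing not at random, we will use methods that explicitly model this type of nonrandom missingness", with pattern-mixture models as the example. The same sentence goes on to "perform sensitivity analyses evaluating the impact of the missingness", so the sensitivity analyses depend on the same finding.

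No criterion is given for reaching the MNAR finding, and no sensitivity analysis is said to run whatever the diagnosis. The diagnosis belongs to the preliminary analyses, the biostatistician receives masked data, and "Randomization will be unmasked only after analyses are finalized".

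Two other sections matter. Under Outcome measures, where the ISI is the primary patient-centered measure: "The battery will be completed through the NOCTEM app at baseline, post-treatment, and again 3 and 12 months post-treatment". Under Intervention, the list of ways a patient's participation ends opens: "1) they decide to stop using the app; or (2) their provider deems that a different treatment or referral is required".

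**The concern.** The rule asks the data a question they cannot answer. MCAR can be contradicted by showing that missingness depends on recorded variables. Whether missingness also depends on the unrecorded outcome, given what was recorded, involves only values nobody has seen. An analyst who follows the text literally never reaches the MNAR branch on evidence.

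Two outcomes are left. Either the MNAR models and sensitivity analyses are run because someone judges MNAR likely, or the data are treated as MAR and the 6-week ISI comparison is reported with no check on that assumption.

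The check is worth having in this trial. A patient who stops using the app, or whose provider refers them elsewhere, may be doing worse than one who stays. The Intervention section adds that the app is disabled once the patient leaves the provider's care. Facilitation acts on providers, so retention could also differ by arm. These are reasons for plausibility; the article reports nothing that shows it.

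**Working it through.** **1. Can the trigger be met?** Take one set of response indicators and observed outcomes, and complete it in two ways. In the simulated example (200,000 patients), response depends on an observed covariate and 28% of outcomes are missing. Under MAR the unseen outcomes follow the same regression as the seen ones. Under MNAR they are 0.5 SD lower.

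| | MAR | MNAR (−0.5 SD) |
|---|---|---|
| Observed-data log-likelihood | −297471.1955 | −297471.1955 |
| Observed mean | 0.0665 | 0.0665 |
| True full mean | −0.0004 | −0.1404 |

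The full means differ by 0.28 × 0.5 = 0.140 SD, yet everything the analyst can see is identical. This holds by construction, which is the point: any observed data set can be completed either way.

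**2. The plan's own figures, for scale.** Inputs from the statistical section: 8 COAST and 16 COAST+ providers, 36 patients each, intra-class correlation 0.01. The correlation is stated for the non-inferiority calculation; using it for superiority is an assumption.

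- Design effect: 1 + 35 × 0.01 = 1.35.
- Superiority SE: √[1.35 × (1/288 + 1/576)] = 0.084 SD. Detectable difference at 80% power: 2.80 × 0.0839 = 0.235, against the stated 0.232. Power at 0.232 is 0.790, against the stated 0.80.
- Non-inferiority SE: √(1.35 × 2/288) = 0.097 SD. Power at a true difference of 0 is 0.999, against the stated figure above 0.99.

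Both figures reproduce closely; neither is in dispute.

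**3. Size of an unexamined departure from MAR.** Let p be the share missing in a group and δ the amount by which missing patients improve less than the imputation model predicts. The group mean is then overstated by p × δ, so

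bias in (COAST+ − COAST) = p₊δ₊ − p₀δ₀.

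All values of p and δ below are assumptions.

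| Missing COAST / COAST+ | δ (SD) | Bias (SD) |
|---|---|---|
| 30% / 15% | 0.5 in both | 0.075 − 0.150 = −0.075 |
| 30% / 15% | 1.0 in both | 0.15 − 0.30 = −0.15 |
| 15% / 30% | 0.5 in both | 0.150 − 0.075 = +0.075 |
| equal shares | equal | 0 |
| any / 20% | 0.5 in COAST+ only | 0.20 × 0.5 = +0.10 |
| any / 30% | 0.75 in COAST+ only | 0.30 × 0.75 = +0.225 |

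0.075/0.232 = 0.32, about a third of the detectable difference. The sign follows the arm with the larger p × δ. With full data, two-sided significance needs an estimate of about 1.96 × 0.084 = 0.164. A MAR estimate of 0.232 corrected for +0.075 becomes 0.157, just under that line. Corrected for +0.10 it is 0.132, and for +0.225 it is 0.007.

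**4. Non-inferiority.** At a difference of 0 the expected lower bound is −1.96 × 0.0968 = −0.190. An adverse shift of 0.15 moves it to −0.340, still above −0.50. Losing 30% of patients in both arms leaves 25.2 per provider, a design effect of 1 + 24.2 × 0.01 = 1.242 and an SE of √(1.242 × 2/201.6) = 0.111. The bound is then −0.15 − 0.218 = −0.368, again above the margin.

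**The case against.** The strongest reply is that the article limits the damage. The missingness check comes before any hypothesis is tested, on masked data, and allocation is revealed only at the end. A reader might infer that the choice of primary ISI method becomes post hoc. The text does not support that: the same section fixes the ISI models (a mixed model for the change score with a provider effect, and a second for ISI at baseline and 6 weeks), and MI is already named for MAR. Only the missing-data layer is conditional, and the judgement is shielded from knowledge of arm. This stands. Masking does not, however, make the mechanism identifiable.

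Second, the figures in the working are assumed. They would equal the error of a complete-case analysis if δ were the raw deficit. The plan is MI, and the daily sleep logs and weekly symptom, side-effect and sleepiness ratings could explain part of any dropout. This also stands, so δ must be read as what is left after imputation.

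Third, a reader might infer that missing 6-week ISI is in fact related to how patients were doing. The article lists ways participation ends; it does not show that those patients lack a post-treatment ISI. Patients who finish because they are well and patients who give up would push in opposite directions.

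Fourth, delta ranges and imputation details normally belong in an SAP, which is not shown. That is fair for the detail, and it means one cannot say the sensitivity analysis will never be run. It does not rescue the rule: the article states a conditional that cannot be executed, and an SAP that followed it would inherit the fault.

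**Conclusion.** The point holds as a flaw in a stated decision rule. The article makes both the MNAR models and the sensitivity analyses depend on a finding that observed data cannot provide against MAR, and attaches no sensitivity analysis to the branch that will be taken by default. It should be corrected, though it does not invalidate the planned ISI models.

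The size is unknown because no missing rate is given. Under the assumed rates, the superiority contrast moves by 0.075 to 0.15 SD in either direction, against a stated detectable difference of 0.232. It does not move at all if shares and residual deficits are equal across groups. A large deficit confined to one group would matter more.

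A reader might also infer that the non-inferiority conclusion is equally at risk. It is not: with the article's inputs and a true difference of 0, a 0.15 SD shift leaves the lower bound near −0.34, well clear of −0.50. The exposure lies mainly in the 6-week superiority comparison.

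**What to change.** Replace the conditional rule with a fixed one.

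- **Primary approach, set in advance:** the mixed models already described, with multiple imputation under MAR that respects clustering of patients within providers.
- **Sensitivity analysis, always run:** a delta-adjusted (pattern-mixture) or tipping-point analysis, with the departure from MAR allowed to differ by arm, for the 6-week ISI superiority comparison. Report it for non-inferiority as well.
- **Role of the missingness investigation:** to describe patterns and choose auxiliary variables, such as the daily logs and weekly ratings already collected. It should no longer decide which method is used.

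The delta range can be left to the SAP; the commitment to run the analysis whatever the diagnosis should replace the current sentence. The cost is a change of wording and modest extra programming, with no new data.
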